## Abstract

**Background:**

Black/African American cisgender women (hereafter referred to as “Black women”) experience one of the highest incidences of HIV yet are often not prioritized in HIV prevention initiatives. For example, pre-exposure prophylaxis (PrEP) for HIV prevention continues to be under-prescribed to women despite its proven effectiveness and demonstrated impact on mitigating HIV transmission. Increasing PrEP initiation and persistence among women through tailored implementation strategies remains crucial to HIV prevention efforts, yet few studies have been designed for women, particularly within the context of family planning centers. This article outlines the study protocol to evaluate the effectiveness of implementation strategies (“EUPHORIA”) to improve PrEP care continuum outcomes and to address barriers to PrEP uptake among women in family planning centers in Cook County, Illinois.

**Methods:**

This study builds upon previous work to adapt implementation strategies for increasing PrEP uptake among Black women. The intervention will consist of implementing a combination of strategies and measuring the impact on PrEP utilization among Black women at 8 family planning centers via a stepped-wedge cluster randomized trial. A mixed-methods approach will be utilized to evaluate implementation outcomes and assess the feasibility, acceptability, and effectiveness of the strategies.

**Discussion:**

As a result of the intervention, we anticipate that Black women within selected health centers will be more likely to receive PrEP prescriptions. During post-implementation analysis, we will identify key barriers and facilitators within the PrEP care continuum during the implementation process at the patient, provider, and system levels. This study contributes to addressing the inequity in PrEP delivery, aiming to increase initiation and persistence of PrEP for women in family planning centers. If determined effective, these implementation strategies will be further disseminated for use in similar family planning health centers and for future study in potential scale-up.

## Introduction

Black women experience one of the highest incidences of HIV in the United States yet are often not prioritized in HIV prevention efforts [1,2]. In the U.S., women account for approximately 20% of annual HIV diagnoses [3]. Twenty-three percent of all people living with HIV (PWH) are women, with heterosexual contact accounting for 86% of all transmission among women [3]. Black women represent only 13% of the national population yet account for 60% of new HIV infections among women [4]. Moreover, the rate of new HIV infections among Black women is 20 times higher than that of White women [4].

Additionally, the prevalence of HIV is high in urban areas of the Midwest, including Chicago, where the prevalence of Black women living with HIV is almost 15 times higher than White women [2]. Chicago has multiple community areas that represent a concentrated HIV epidemic, with prevalence consistently over 5% [5]. Women in these areas of Chicago remain vulnerable to HIV, even while transmission rates among women remain steady or decline throughout the U.S.

Pre-exposure prophylaxis (PrEP) has been proven to be beneficial and provide substantial protection against HIV; however, uptake among Black women has been disproportionately low. In 2015, the Centers for Disease Control and Prevention (CDC) estimated that up to 500,000 Black women in the U.S. may be eligible for PrEP based on CDC clinical guidelines, yet Black women are severely under-prescribed PrEP compared to White women [6]. Specifically, pharmacy records show that fewer than 50,000 women have initiated PrEP since 2012 when it was first approved, with less than 7,000 (14%) of those being Black women [5–7].

Our team developed and tailored implementation strategies for optimizing PrEP uptake utilizing previously identified barriers and facilitators to PrEP uptake [8–10]. Patient-level barriers included low PrEP awareness, concerns about side effects, potential impacts on fertility and pregnancy, and uncertainty about how to pay for PrEP. Provider-level barriers included lack of PrEP-specific training, need for additional clinical support for PrEP protocols, and need for additional training to increase comfort discussing PrEP with patients [8]. Health center-level implementation strategies, such as HIV prevention with family planning services, routine PrEP education for patients, standardized provider training, electronic health record (EHR) tools, PrEP navigation, and on-site clinical champions, offer a structural intervention for both patient and provider barriers. This specific set of strategies has yet to be implemented and evaluated in the context of family planning centers. Furthermore, family planning centers that provide contraception and sexually transmitted infection (STI) prevention services may be an underutilized context where women can successfully transition from awareness to initiation of PrEP. Linkage to PrEP in the context of family planning centers is critical, as the majority of women who are diagnosed with HIV in a given year are of reproductive age (i.e., 15–44 years of age) [4].

Our proposed study will implement and evaluate the impact of these adapted implementation strategies (hereafter referred to as “EUPHORIA”) within the Planned Parenthood of Illinois (PPIL) setting to improve PrEP care continuum outcomes for Black women. By identifying, adapting, and evaluating implementation strategies in PPIL health centers, we seek to address the gap in knowledge in determining effective strategies to increase uptake of PrEP among Black women.

## Materials and methods

### Aims and objectives

This study seeks to evaluate implementation strategies to address barriers and increase uptake of PrEP among women in PPIL through three specific aims. Aim 1 will adapt the PrEP implementation strategies for engaging Black women in the PrEP care continuum in eight PPIL centers. Adaptations will be informed by qualitative data collected through interviews and focus groups with PPIL administrators, staff, providers, and patients and guided by the Dynamic Adaptation Process (DAP) [11]. Aim 2 will implement the strategies that are identified in Aim 1 and tailored accordingly via a stepped-wedge cluster randomized trial (SW-CRT) across the eight PPIL center sites. Aim 3 will assess and document implementation outcomes and report on key barriers and facilitators related to the implementation of the intervention.

A mixed-methods approach including focus groups and interviews with key stakeholders will be used to evaluate implementation outcomes. This evaluation will be guided by the Reach, Effectiveness, Adoption, Implementation, and Maintenance (RE-AIM) framework and the Consolidated Framework for Implementation Research (CFIR). Findings will provide insight into implementation strategies that can support effective replication across Planned Parenthood health centers and other health centers providing family planning services nationwide to reach a greater number of Black women at risk. This study was approved by the Institutional Review Board at Rush University Medical Center (#21120602).

### Guiding theories and frameworks

The Social Ecological Theory is the guiding theory that underlies EUPHORIA. This theory highlights that an individual’s behavior and health-related decisions are embedded in an intersectional context (provider, health center, etc.) [12]. Research has consistently shown that barriers within healthcare are driven and sustained by multi-level factors and interventions that fail to consider such overlapped levels will likely fall short of achieving a comprehensive understanding of the drivers of health disparities [13–15]. The Social Ecological Theory can be leveraged to identify high-impact points within health centers and center task flow that can facilitate the successful implementation of interventions. Our proposed implementation strategies to support PrEP uptake among women address multiple levels including the individual (patient education), provider (provider training), health center system (EHR tools), and broader health system (PrEP navigation, clinical champion) (Table 1).

**Table 1 pone.0355623.t001:** EUPHORIA intervention package of strategies.

Strategy	Description
Routine PrEP education	PrEP education provided at each clinic visit to all Black women
Standardized provider training	3 sessions of 2-hour virtual trainings covering identifying PrEP-eligible women, working with the PrEP navigator/navigation team, and practicing difficult conversations with virtual Black women patients (avatars)
EHR tools	Incorporate the PrEP indication documentation into the EHR; provide monthly reports of PrEP continuum outcomes for clinic staff
PrEP navigation, clinical champion	Trained PrEP navigator to meet with patients to support PrEP uptake, monthly check-in with patients thereafter to support retention and adherence; follow-up appointments offered in-person or via telehealth; PrEP expert who can guide clinicians in implementing the EUPHORIA strategies

PrEP: Pre-exposure Prophylaxis; EHR: Electronic Health Record

This study will also utilize the Consolidated Framework for Implementation Research (CFIR). CFIR consists of five inter-related domains: intervention characteristics, outer setting, inner setting, characteristics of individuals involved, and the process of implementation [16]. CFIR accounts for the non-linear process of implementation and incorporates consideration of the adaptation that is required for different contexts, making it a useful framework for this study [17]. Moreover, as our study focuses on a specific, marginalized, and often overlooked population, we propose to integrate health equity domains across multiple levels of CFIR [18,19]. Health equity domains focus on multilevel factors in healthcare disparities with an emphasis on unique factors that populations experience due to social and historical marginalization, including: 1) cultural factors of recipients, 2) patient-provider interaction, and 3) societal context (including but not limited to social structural determinants of health) [20].

The Reach, Effectiveness, Adoption, Implementation, and Maintenance (RE-AIM) framework is an evaluation and reporting scheme commonly used to examine the public health impact of an intervention [21]. RE-AIM provides a useful measurement framework for capturing both clinical and implementation outcomes within the same study [22,23]. Integrating CFIR with Health Equity domains and RE-AIM within a hybrid clinical effectiveness-implementation trial will generate the evidence needed to rapidly translate our findings to standard practice.

### Setting

EUPHORIA implementation strategies will be adapted and implemented in eight PPIL health centers (Table 2). All study sites are located within Cook County, Illinois, which is a priority jurisdiction of the CDC’s Ending the HIV Epidemic (EHE) initiative [24]. These sites were chosen due to their area’s heightened HIV burden as identified by the EHE initiative and the higher volume of PrEP-eligible Black women within their patient population. All participating PPIL health centers currently have low PrEP usage (<1%) among Black women who receive care at their sites. Additionally, these sites were selected due to their varied locations within Cook County and subsequently, varied contextual factors (e.g., prevalence rates of HIV and other STIs, economic hardship index scores, etc.). By adapting and implementing the proposed strategies in multiple distinct neighborhoods within Cook County, we aim to assess the consistency and discrepancy of implementation outcomes across sites, increasing applicability of findings to a broader range of settings through exploration of site-specific contextual elements.

**Table 2 pone.0355623.t002:** Participating health centers and corresponding patient volume in calendar year 2023.

Planned Parenthood of Illinois Health Center	Number of unique Patients	Volume of patients who are women	Volume of patients who are Black women
Heath Center 1	3,532	2,046 (57.9%)	224 (6.3%)
Health Center 2	4,732	2,889 (61.1%)	438 (9.3%)
Health Center 3	3,462	1,128 (32.6%)	224 (6.4%)
Health Center 4	4,611	870 (30.2%)	144 (3.1%)
Health Center 5	10,214	3,970 (38.8%)	502 (4.9%)
Health Center 6	3,849	2,584 (67.1%)	518 (13.5%)
Health Center 7	4,293	1,457 (33.9%)	217 (5.1%)
Health Center 8	2,838	857 (18.8%)	144 (5.1%)

### Study design

EUPHORIA will use a SW-CRT to measure changes in the number of PrEP prescriptions initiated among Black women accessing PPIL services who are eligible for PrEP (primary clinical outcome) and the receipt of PrEP refills among those who initiate PrEP (secondary clinical outcome). In a stepped-wedge study, each health center provides observations to the control condition (standard of care) and the intervention conditions [20–22]. Each cluster switches from the control to the intervention condition at regular intervals or “steps”. The step (time point) at which a health center switches from control to intervention is randomly assigned [25]. The stepped-wedge design provides a pragmatic and robust approach to testing the effectiveness of health service delivery interventions [26]. This approach’s pragmatism arises from the rollout of the intervention over time, which enables study staff to support the implementation of a multi-pronged intervention at multiple study sites within a randomized design and increases study sites’ willingness to participate because all health centers receive the intervention during the study period. The stepped-wedge design is robust due to each cluster providing data under both the control and intervention conditions and, therefore, serving as its own control. This design improves the precision of the study and allows for intervention effectiveness to be measured across sites with different characteristics. Varied durations under the control and intervention conditions and randomly assigned transition timing enhance the statistical power in this design to differentiate intervention effects from underlying time trends.

In our stepped-wedge design (Fig 1), each step is three months long, and there are eight waves of intervention implementation, with one site beginning the intervention at each step [20]. The eight participating PPIL health centers will be randomized to a step, at which time they will implement the intervention. Baseline (non-intervention) data in all sites will be collected for three months prior to the first intervention step. Each health center will also undergo a three-month transition period when the health center prepares to implement the intervention package and outcome data are treated as occurring in neither the control nor intervention period.

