#### Implementation and post-implementation phases.

All outcome data to be collected are part of existing routine EHR data collection at PPIL. PPIL Information Technology (IT) will create custom reports in the PPIL data warehouse to be built utilizing the existing data fields and a table of desired variables (Table 3).

**Table 3 pone.0355623.t003:** Requested electronic health record variables within limited data set.

Data domain	Brief description
Denominator/overall PrEP eligibility	Number of patients who are eligible to learn more about and receive PrEP according to study criteria: all patients 12 years or older, who are not living with HIV, and who have had a relevant medical encounter (e.g., family planning, sexual health care, primary care, etc.) during which PrEP could be prescribed *PrEP ineligibility: Patient is less than 12 years old or is medically unable to use PrEP (e.g., living with HIV) or attends a medical encounter during which PrEP is unlikely to be discussed or prescribed.
PrEP eligibility characteristics	STI screening history, risk factors, prior PrEP visits, and HPI for PrEP, visit date, visit type, location of care
Primary and secondary outcome measures	
PrEP initiation (i.e., initial prescription) – primary outcome	Proportion of Black women at each site who receive an initial prescription for PrEP (i.e., have not received a prescription for PrEP in the prior six months)
PrEP persistence (i.e., subsequent/refill prescription) – secondary outcome	Proportion of Black women at each site who receive a subsequent prescription of PrEP after initiating PrEP (i.e., refill initial prescription within six months)
Process measures	
HIV risk assessment	Proportion of eligible Black women who undergo HIV risk assessment at each site
PrEP education	Proportion of eligible Black women who receive PrEP education at each site
PrEP navigation	Proportion of eligible Black women who are referred to PrEP navigator at each site
Sociodemographic data/covariates	Gender identity, sex assigned at birth, sexual orientation, race, ethnicity, date of birth, gravidity, parity, annual income, preferred language, home zip code, marital status, disability status, HIV status, STI testing and diagnosis history within past year, location of care, prescription name(s) and duration(s)

PrEP: Pre-exposure Prophylaxis; STI: Sexually Transmitted Infection; HPI: History of Present Illness

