Reports will be built to monitor (1) EHR alert consistency, (2) if PrEP is offered, (3) if PrEP is accepted or declined, and (4) among those who accept, if patient navigation is utilized and if PrEP is prescribed. These data will be collected at the health center level and during two phases: 1) the control, or baseline phase and 2) the intervention phase. The control and intervention phases are of variable length depending on step assignment (Fig 1). Implementation outcomes of each health center will be assessed at the midpoint and endpoint of the intervention period.

The initiation of PrEP prescriptions for eligible Black women (primary clinical outcome) will be measured using de-identified patient-level EHR data. Eligibility for inclusion in the outcome measures among patients will be determined based on study inclusion criteria such as patient’s age, biological sex and gender identity, and race. The primary outcome will be the proportion of eligible Black women at each health center who receive a prescription for PrEP during that month. The secondary outcome will be PrEP refills within six months, i.e., receipt of a PrEP prescription within six months of the index visit among those in the eligible population with a prior PrEP prescription. Finally, the total number of PrEP prescriptions among all patients in the control (baseline) and intervention periods will be analyzed to determine the impact of the implementation strategies on the entire PPIL patient population.

At approximately the midpoint of each site’s intervention period, key informant interviews including focus groups and interviews will be conducted with PPIL staff, clinicians, and women to assess implementation outcomes such as acceptability, feasibility, and fidelity over time. These interviews will elicit information related to the barriers and outcomes encountered during implementation. Procedures for recruitment and enrollment for these participants will mirror those of pre-implementation qualitative data collection completed as part of Aim 1. Data will be coded according to the RE-AIM constructs, with emerging themes identified and categorized by implementation outcome: acceptability, feasibility, and fidelity (Table 4). The usage of mixed methods in this study will be used to elaborate on quantitative RE-AIM findings with themes from qualitative data. Participant recruitment and data collection are expected to be completed by June and December 2028, respectively.

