#### Sample size.

This study will be powered to determine whether there is a statistically significant difference in PrEP prescriptions among at-risk Black women defined as those with a positive STI test accessing family planning services between the intervention and control periods. We choose to use presenting to a family planning clinic and a positive STI test (gonorrhea, chlamydia, or syphilis) as eligibility to ensure patients at high risk for HIV acquisition are offered PrEP within the PPIL context, keeping in line with the CDC’s guidance to offer PrEP to patients at substantial risk of HIV acquisition. A power calculation was conducted based on a mixed effects effectiveness model with a random intercept for clinic and intervention and time as fixed effects. Assuming a baseline PrEP uptake of 1% and a conservative intraclass correlation coefficient (ICC) of 25%, a trial with 10 PrEP-eligible Black women per month (30 women per step) at each of the 8 clinics (8 steps) would allow us to detect an increase to 5% PrEP uptake (corresponding to an odds ratio of 5.21 for the intervention effect) in eligible Black women following the introduction of the intervention with >90% power at a two-sided alpha of 0.05. Our sample size provides almost 100% power for detecting a larger increase to 15% PrEP uptake (corresponding to an odds ratio of 17.47 for the intervention effect). Our sample size accounts for both the clustered nature of the design and the potential confounding effect of time. We used R software for power analysis.

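### The secondary persistence outcome is defined among women the intervention itself brings onto PrEP, its denominator is worded three ways, and control initiators will probably be few

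*Protocol article*

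**What the plan says.** The Protocol article describes the persistence outcome in three places.

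- **Study design:** the stepped-wedge trial measures changes in PrEP initiation (primary) and "the receipt of PrEP refills among those who initiate PrEP (secondary clinical outcome".
- **Implementation and post-implementation phases, text:** "receipt of a PrEP prescription within six months of the index visit among those in the eligible population with a prior PrEP prescription". This can include women already established on PrEP.
- **Same section, Table 3:** "Proportion of Black women at each site who receive a subsequent prescription of PrEP after initiating PrEP", with a six-month limit for the refill.

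Under Sample size, baseline uptake is 1% and the targets are 5% and 15%. The power statement covers prescriptions only, and no expected number of initiators is given. Under Setting, "All participating PPIL health centers currently have low PrEP usage (<1%) among Black women who receive care at their sites".

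Under Quantitative data, refill rates are to be plotted over time. One mixed model for the treatment effect is then described (random site intercept, fixed effects for intervention and time interval, identified confounders) without naming the outcome it serves. Selection into initiation is not discussed. The abstract's Discussion gives higher initiation and higher persistence as the purpose of the work.

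**The concern.** Initiation is the primary outcome, and the package is built to increase it. Restricting the refill comparison to women who have initiated conditions on something that happens after randomisation and that the intervention affects. Control initiators are the few who obtain PrEP under standard care. Intervention initiators are women of that kind plus a larger group reached through education and navigation. Randomising the step order makes eligible women comparable in expectation, after allowing for time, but not initiators.

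The package could therefore appear to lower persistence while more women stay on PrEP, or the reverse. Because it also includes monthly navigator check-ins aimed at retention (Table 1), a real persistence effect could be hidden or exaggerated by the change in mix. The results are meant to inform scale-up. In addition, three wordings of the denominator can give three different rates from the same records.

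**Working it through.** **1. The plan's own figures.** Odds ratio for 1% to 5%: (0.05/0.95)/(0.01/0.99) = 5.21. For 1% to 15%: (0.15/0.85)/(0.01/0.99) = 17.47. Both match Sample size. The stated power above 90% for 5% also reproduces (90.9%, logit-scale generalised least squares) in a nine-period wedge with no transition gap. With the transition quarter left out, the same method gives 78–82%. All of this concerns prescriptions; there is no corresponding figure for refill.

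**2. How far the denominator changes.** Suppose everyone who would start under standard care also starts under the package. At 5% uptake, (5 − 1)/5 = 80% of intervention initiators would not have started under control. At 15% it is 14/15 = 93%.

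**3. What that can do to the contrast.** The documents give no refill rates, so these are assumed.
- Self-starters refill at 60% in both conditions, prompted women at 30%, uptake 5%: refill among initiators is (0.01×0.6 + 0.04×0.3)/0.05 = 36%, down from 60%. The share of all eligible women who start and refill rises from 0.6% to 1.8%.
- Self-starters 70%, prompted women 50%, no effect on anyone's persistence: (0.7 + 4×0.5)/5 = 54% at 5% uptake, a false drop of 16 points. At 15% uptake, (0.7 + 14×0.5)/15 = 51%, a false drop of 19 points. Swapping the two rates reverses the sign.

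**4. Expected control initiators.** Nine three-month periods (27 months), one site per step, transition quarter excluded. Depending on where the transition falls, control time is 3×(0+…+7) = 84 or 3×(1+…+8) = 108 site-months, that is 28 or 36 site-quarters. Women per site-quarter: 30 (Sample size: "10 PrEP-eligible Black women per month (30 women per step) at each of the 8 clinics (8 steps") or, from Table 2, 2,411/(8×4) = 75.3, counting each woman once a year.

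| Women per site-quarter | 28 site-quarters | 36 site-quarters |
|---|---|---|
| 30 | 28×30×0.01 = 8.4 | 36×30×0.01 = 10.8 |
| 75.3 | 28×75.3×0.01 = 21.1 | 36×75.3×0.01 = 27.1 |

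If 1% is instead the rate in a typical clinic with ICC 0.25, simulation at 30 per step gives a mean of about 14–17, inside the same range.

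**5. Precision.** Exact 95% intervals for a control refill rate: 5 of 10 gives 19–81%; 13 of 27 gives 29–68%.

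Approximate power in the planned type of model (logit scale, period effects, site intercept, transition excluded, ICC 0.05–0.25, intervention uptake 5% or 15%), with control refill assumed at 50%:

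| Refill compared | 30 per quarter | 75.3 per quarter |
|---|---|---|
| 50% v 60% | 6–7% | 8–10% |
| 50% v 70% | 11–15% | 20–30% |
| 50% v 80% | 22–32% | 42–64% |
| 50% v 90% | 40–61% | 71–93% |

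Ignoring clustering and time, the smallest difference detectable with 80% power is about 36–41 points with 8–11 control initiators and 26–29 points with 21–27.

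**The case against.** Refill among initiators is a legitimate care-continuum measure. The article claims power only for prescriptions and does not say outright that the mixed model will be fitted to refills; the condensed format may leave that to a fuller plan. What stands against this is that Study design lists refills among the outcomes whose change the randomised design is to measure, and that the denominator is fixed in the text. Adjusting for measured confounders does not restore comparability, since no variable listed in Table 3 directly captures motivation to start PrEP.

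Table 3 can be read with all Black women at the site as denominator, which would remove the selection problem. That is a possible reading, not a clear contradiction of the other two places, and it strengthens the case for reconciling them.

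The range of 8 to 27 is not a figure in the article. The low end uses the women with a positive STI test from Sample size, whereas Table 3 eligibility is broader. The high end counts each woman once a year, although the primary outcome is monthly. The period covered by the 1% is not stated, and women with earlier prescriptions are not counted. The timeline figure is not shown, and either transition placement inside 27 months leaves one site without control or without intervention data. These objections are fair: the count is an order of magnitude.

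The remedy is also open to challenge. An initiate-and-refill proportion can rise solely because initiation rises, as in the 60%/30% example. That is why it should be added beside refill among initiators and should not replace it.

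**Conclusion.** The point holds in a limited form. Under two of the three wordings, the between-condition refill comparison is made in a group that the intervention changes. It cannot separate a different mix of women from different persistence. This follows from the definitions and needs no assumed rate; the size and direction of the bias are unknown.

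Few control initiators are likely. About 8 to 27 rests on three assumptions: 1% per woman counted, the choice of denominator, and the transition placement. The power figures also assume a 50% control refill rate. On that basis, differences of 10 to 20 points would be poorly estimated.

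A reader might infer that the persistence question is unanswerable or that the model can hardly be fitted. The documents do not support that. At the Table 2 volume a difference of 40 points could be detected with 71–93% power, and the random site intercept pools information across sites. Nor do they support saying that the bias must run downward. Since this is a secondary outcome, the plan should be changed, but the primary comparison is not affected by this point.

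**What to change.** 1. Bring Study design, the implementation-phase text and Table 3 to one definition of the persistence denominator. State which condition a refill is credited to when the six-month window, which spans two steps, crosses a site's change of condition.
2. Add, as the between-condition persistence outcome, the proportion of all eligible Black women (the primary outcome's denominator) who initiate PrEP and receive a subsequent prescription within six months.
3. Keep refill among initiators as a descriptive care-continuum measure by condition, with a statement that it is not a randomised comparison.

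The cost is wording and one derived variable from EHR data already requested. The downside is real: the added outcome partly reflects initiation and will have few control events (at an assumed 60% refill, 8.4×0.6 = 5 to 27.1×0.6 = 16). It must be read beside the initiation rate and the refill rate among initiators, and not as evidence of better persistence among PrEP users.
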